### Procedure

Study flow is presented in Fig. 3 and the schedule of enrolment, interventions, and assessment (SPIRIT figure) in Fig. 4. The Trial Registration Data checklist and SPIRIT checklist can be found in Additional files 1 and 2, respectively.

**Fig. 3 Fig3:**
[figure not shown]
Study flow. SE, Self-efficacy enhancement module; SS, Social support enhancement module

**Fig. 4 Fig4:**
[figure not shown]
Schedule of enrolment, interventions, and assessments

Participants will be recruited via targeted Facebook ads, the project’s website and through promotion in the regional and national media. Interested participants will be invited to visit the intervention public page (medstres.pl) and watch a short video clip in which the project’s team explains the purpose and scope of the study. Subsequently, they will be asked to declare whether they are at least 18 years old, represent medical professions, and have access to an Internet-connected device; all in order to check whether they are eligible to participate. Upon registration, participants will be asked to provide informed consent. All registration procedures will be conducted online, with no contact from the research team. The implications of participation in the study will be clearly explained in the materials (text and a video clip) on the public website and in the informed consent document. This process was approved by the research ethics committee. After accepting to be randomized to one of four study conditions, participants will be asked to fill out the baseline questionnaires (pretest). Once those are completed, participants will be randomized and allocated with a 1:1:1:1 ratio to one of four study conditions. The registration process is continuous, which means that access to the Med-Stress program is given instantly, but the content is released on Mondays. Every week a new exercise is available and participants will be notified via e-mail. Such a recurrent design is determined by the task that requires participants in three conditions (those that include a perceived social support enhancement module) to take part in a forum discussion at the same time. Depending on the study condition, the intervention will take 3 weeks (active control conditions) or 6 weeks (experimental conditions). Participants will not be informed about the result of the allocation but it is public knowledge that Med-Stress consists of four variants that differ in terms of length (depending on whether a given variant contains one or two modules) and the type of exercises. Regardless of the condition, all participants have access to four optional modules throughout the study: Relaxation, Mindfulness, Cognitive Restructuring, and Lifestyle. Participants will be asked to fill out questionnaires at four times during the study: before the intervention, posttest (i.e., right after the intervention: at 3 or 6 weeks depending on the study condition), and at 6-month and 12-month follow up. Additionally, users assigned to experimental conditions will undergo mid-intervention assessment. Depending on the first module, perceived social support (one scale) or self-efficacy (two scales: self-efficacy to manage job stress and burnout, and self-efficacy to obtain social support) will be measured. At each assessment point, participants will receive an e-mail notification containing a link to the survey. All measurements throughout the study will be obtained online, which has been shown to be a reliable mode of administering psychological, self-report questionnaires [45]. To ensure a high response rate, each e-mail notification will be followed by two reminders every 2 days. Moreover, we will include supportive messages in the survey between questionnaires, thanking the participants for getting this far and encouraging them to continue until completion. All participants will be advised that should they experience any psychological discomfort, harm, or other unintended effects of the intervention or study, they are encouraged to contact the study team or other mental-health professionals. At any time during the intervention period and after completing the program, the participants have the right to withdraw their participation without the obligation to provide their reasons, as stated in the informed consent.

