**Methods:**

In this four-arm randomized controlled trial we will test four variants of the Med-Stress intervention. The trial is open for professionally active medical providers aged at least 18 years (*N* = 1200) with access to an Internet-connected device. We will compare the effects of two experimental conditions reflecting cultivation and enabling effects of self-efficacy and perceived social support (sequential enhancement of resources), and two active controls strengthening self-efficacy or perceived social support. Job stress and job burnout will be the primary outcomes, whereas depression, job-related traumatic stress, and work engagement will be secondary ones. Additionally, we will measure perceived social support, self-efficacy to manage job stress and burnout, and the ability to obtain social support, exposure to traumatic events, and users’ expectancy and credibility of the intervention. All assessments will be applied before the intervention, at posttest (at 3 or 6 weeks depending on the study condition), and at 6-month and 12-month follow up. In the case of experimental groups, additional measurements will be taken after enhancing each resource.

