### Outcomes

#### Primary outcomes

There will be two primary outcomes in this study: job stress and job burnout.

The Perceived Stress Scale 14 (PSS-14) [2] will be used to measure job stress. We adapted the questionnaire’s instruction to refer to occupational stress. It consists of 14 items with the response scale ranging from 0 (never) to 4 (very often). A higher total score represents higher perceived stress.

The Oldenburg Burnout Inventory (OLBI) [47] will be applied to measure job burnout. It consists of 16 items with the response scale ranging from 1 (strongly agree) to 4 (strongly disagree). The questionnaire consists of two subscales: exhaustion and disengagement. A higher total score represents greater job burnout.

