All the scales will be measured pretest, posttest, and at the two follow ups (at 6 and 12 months). The exceptions are STES and CEQ, which will only be assessed at baseline. All scales included have been validated in Poland and their reliability was tested in a feasibility study with satisfying results, with Cronbach’s alpha between 0.75 and 0.97. Completion of the surveys takes about 20 min.

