### Statistical analysis

We will conduct analyses of covariance (ANCOVA) with condition assignment as a factor, all primary and secondary measures at posttest as outcomes, and their pretest values as covariates. This will allow us to test for group differences between study conditions posttest while controlling for change over time. ANCOVA has been shown to be more parsimonious than analysis of variance (ANOVA) in randomized trials with a repeated measures design, and thus to have more power [56]. In terms of specific analyses, primarily, we will compare the effects of experimental conditions to each active control to test whether a two-module intervention is more effective that a single-module one. Next, we will compare the effects of the two experimental conditions to check if the sequence of the modules contributes to the intervention effects. Bonferroni’s adjustment for multiple comparisons (five comparisons and five outcomes) will be applied, which will lower the *p* levels to .002 for detection of the effects. Additionally, we will conduct separate ANCOVA to test whether the differences in outcomes between study conditions are maintained at the 6-month and 12-month follow up. Furthermore, we will conduct mediation analyses to verify the hypothesized mechanism of the effect of condition assignment on the primary and secondary outcomes. Sequential mediation analyses will be applied using the PROCESS macro [57] with condition assignment as a predictor, primary and secondary measures posttest as the outcomes, their baseline scores as covariates, and self-efficacy and perceived social support posttest as mediators (see Figs. 1 and 2 for conceptual models of mediations).

Additionally, we will carry out moderation analysis to test whether the initial (pre-intervention) expectancy about the positive outcomes of the treatment (i.e., how successful the intervention would be in reducing stress and burnout symptoms in participants’ opinions) moderates the relationship between the condition assignment and the study outcomes. As participants in the study will have the option of engaging in one or more out of four additional modules, we will consider participation in them as a control variable.

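### Job stress and burnout are measured at week 6 in the experimental arms but at week 3 in the active controls, so the four two-module versus one-module posttest comparisons are confounded with elapsed time

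*Protocol article*

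**What the plan says.** All points are in the protocol article.

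- **Programme length (Procedure).** "Depending on the study condition, the intervention will take 3 weeks (active control conditions) or 6 weeks (experimental conditions".
- **Timing of posttest (Procedure).** Questionnaires are due before the intervention, at "posttest (i.e., right after the intervention: at 3 or 6 weeks depending on the study condition"), and at 6 and 12 months. The Abstract repeats the rule: "at posttest (at 3 or 6 weeks depending on the study condition").
- **Mid-intervention assessment (Procedure).** Only the experimental arms have one, and it covers the resource scales: "Depending on the first module, perceived social support (one scale) or self-efficacy (two scales: self-efficacy to manage job stress and burnout", plus self-efficacy to obtain support). Job stress and burnout are not on it.
- **Schedule of scales (Other measures).** "All the scales will be measured pretest, posttest, and at the two follow ups (at 6 and 12 months"), with two baseline-only exceptions. No week-6 assessment of the controls is listed.
- **Primary outcomes.** "There will be two primary outcomes in this study: job stress and job burnout", measured with PSS-14 and OLBI.
- **Analysis (Statistical analysis).** "We will conduct analyses of covariance (ANCOVA) with condition assignment as a factor, all primary and secondary measures at posttest as outcomes", with pretest values as covariates. On the order of testing: "primarily, we will compare the effects of experimental conditions to each active control". The comparison of the two experimental arms comes next. The section also says that this model tests group differences with change over time controlled for. Separate ANCOVAs at 6 and 12 months ask whether differences persist.
- **Optional modules (Procedure).** All arms have access to relaxation, mindfulness, cognitive restructuring and lifestyle exercises.

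**The concern.** Randomisation makes the arms comparable at any given time after allocation. It does not make one arm at week 6 comparable with another at week 3. Whatever happens to job stress and burnout between those weeks, apart from the second module, enters the experimental-versus-control difference and is read as the benefit of the second module.

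Three routes are plausible from the text:

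- Natural change after enrolment has twice as long to run in the experimental arms.
- Those arms have 3 more weeks of access to the optional modules before they are measured.
- In the other direction, the controls are measured just after their only module. In the experimental arms the first module ended 3 weeks before posttest, so its effect may have faded.

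The contrast at stake is the central one. The Background calls the comparison of the two experimental arms explorative, so every directional hypothesis at posttest rests on the four affected comparisons, for both primary outcomes.

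**Working it through.** **1. When each arm answers the primary scales**

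| Arm | Pretest | Week 3 | Week 6 | Months 6 and 12 |
|---|---|---|---|---|
| Two modules (both orders) | PSS-14, OLBI | first-module resource scale(s) only | PSS-14, OLBI (posttest) | PSS-14, OLBI |
| One module (both controls) | PSS-14, OLBI | PSS-14, OLBI (posttest) | nothing scheduled | PSS-14, OLBI |

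Before month 6 there is no column after pretest in which all arms answer the primary scales.

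**2. Which comparisons are affected**

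There are 2 experimental arms × 2 controls = 4 comparisons at week 6 versus week 3, and 1 comparison (experimental versus experimental) at week 6 versus week 6. Four of five are affected.

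**3. Why the pretest covariate does not help**

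Suppose posttest = a + b × pretest + effect of arm + g(t) + error, where g(t) is change at time t that would occur without the second module. Then t = 6 in both experimental arms and t = 3 in both controls. The ANCOVA contrast estimates the second-module effect plus g(6) − g(3). The covariate removes chance differences in starting level. It carries no information on g(6) − g(3), and time is fixed by arm, so no model fitted to posttest data can estimate the two parts separately.

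**4. The plan's own sample-size figure**

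The inputs (Sample size section) are 4 conditions, α = 0.05/25 = 0.002 and power 0.90. For an ANCOVA with one covariate, numerator df 3 and noncentrality N × f², taking f = 0.20 gives N = 607, as stated. The text labels the effect d = 0.20, but 607 follows from f = 0.20. For two arms against two, f = 0.20 corresponds to d = 0.40. The timing problem changes neither 607 nor 1200. The label matters only for the yardstick in step 5.

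**5. How large could the effect be?**

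The documents give no figure for change between weeks 3 and 6, so this step rests on assumptions:

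- Extra change B = g(6) − g(3) of 0.03 to 0.15 SD, which is 0.01 to 0.05 SD per week × 3 weeks.
- No true benefit of the second module.
- Pretest-posttest correlation r = 0.6, or no gain from the covariate (r = 0).
- 300 per arm, as planned.

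SE = √(1 − r²) × √(2/300). With r = 0 this is 0.0816; with r = 0.6 it is 0.8 × 0.0816 = 0.0653. The two-sided critical value at 0.002 is z = 3.090. The rejection probability is Φ(B/SE − z) + Φ(−B/SE − z).

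| Assumed B (SD) | r = 0.6 | No covariate gain |
|---|---|---|
| 0 | 0.002 | 0.002 |
| 0.05 | 0.010 | 0.007 |
| 0.10 | 0.060 | 0.031 |
| 0.15 | 0.21 | 0.105 |

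Worked example for B = 0.15, r = 0.6: 0.15/0.0653 = 2.296, and Φ(2.296 − 3.090) = Φ(−0.794) = 0.21. At B = 0.03 and r = 0.6 the result is about 0.004, little above nominal. With 165 per arm (300 less the top of the article's dropout range, 45%) and r = 0.6, B = 0.15 gives about 0.08.

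Against d = 0.20 the assumed range is 0.03/0.20 = 15% to 0.15/0.20 = 75%. Against d = 0.40 it is half that, about 8% to 38%.

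If B runs the other way, it hides a real effect. With r = 0.6, 300 per arm and a true difference of 0.20, power per comparison is 0.489 without bias and 0.059 if B takes away 0.10.

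**The case against.** **End-of-programme assessment is a recognised design.** The trial compares whole variants whose length is openly part of the package, and measuring each arm on completion equalises the time since last content. That is coherent, but the article does not argue it. It attributes the contrast to targeting two resources rather than one, and it says change over time is dealt with. A common time from the start also keeps programme length, and any fading, inside the treatment effect, so the package question can be answered there too.

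**The 6- and 12-month analyses compare the arms at nominally common times.** This is true and gives some protection, since a short-lived artefact should not persist. But they are planned as tests of maintenance and do not replace the posttest comparison.

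**A week-6 assessment favours the arms that have just finished.** This stands in part: the controls would be 3 weeks past their last exercise. That is a real consequence of a shorter programme, but it must be stated when the result is interpreted.

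**Some readings go further than the text allows.**

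- A reader might count repeated measurement as a source of bias. By posttest every arm has answered PSS-14 and OLBI exactly twice, so it is not.
- A reader might presume strong regression to the mean. Entry has no stress or burnout threshold, so this is possible through self-selection but not shown.
- A reader might presume a seasonal trend. Registration is continuous, so it need not accumulate in one direction.
- A reader might infer unequal non-response. The documents do not show it, and the plan has multiple imputation and a dropout analysis.
- A reader might fault the anchor of the later follow-ups. It is merely unstated in a condensed article.

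**Conclusion.** The point holds for the four posttest comparisons of an experimental arm with an active control. It does not touch the comparison of the two experimental arms. The confounding is a matter of the schedule and needs no assumption: posttest time and number of modules are the same variable. It follows that the sentence in Statistical analysis about controlling change over time is incorrect as written.

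The size and direction of the bias are unknown. The range of about 0.004 to 0.21 for the false-positive rate per comparison rests on an assumed extra change of 0.03 to 0.15 SD, an assumed r of 0.6 and 300 analysed per arm. The top value falls to about 0.105 with no covariate gain, and the bottom value is negligible. These figures show what could happen, not what will.

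A reader might infer that randomisation has failed, or that a positive result would be an artefact of time. The documents support neither. The arms remain randomised; what is unprotected is the difference in elapsed time, and only at posttest. The strict 0.002 threshold does not help, because a multiplicity adjustment limits chance findings and leaves bias in place.

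**What to change.** 1. Give PSS-14 and OLBI, ideally with the other outcome scales, to all four arms at both week 3 and week 6, counted from first content release. Adding week 6 to the controls alone would leave unequal numbers of measurements on the primary scales.
2. Make week 6 the time point of the primary ANCOVA.
3. Keep the end-of-programme comparison (week 3 versus week 6) as a secondary analysis, labelled as such.
4. In Statistical analysis, replace the claim about change over time with a statement that the pretest covariate adjusts for starting level.
5. When interpreting week 6, state that the controls are then 3 weeks past their last exercise.

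**Cost.** About one extra short online survey per participant. The controls gain a week-6 survey, and the experimental arms, which already answer a mid-intervention survey, gain the primary scales there. The article puts survey completion at about 20 minutes; PSS-14 and OLBI alone are 14 + 16 = 30 items. Invitations already go out by e-mail, so the work is a platform setting and an ethics amendment. The added burden matters somewhat in an unguided trial that allows for up to 45% dropout, which is a reason to keep the added survey to the outcome scales. Sample size and intervention content do not change.

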
### Intervention: Med-Stress

Med-Stress is an unguided open access, standalone Internet-based intervention that consists of four conditions: two experimental and two active controls, to which participants will be randomly assigned. In the experimental conditions, participants will complete two obligatory modules (enhancing self-efficacy and perceived social support or perceived social support and self-efficacy), whereas in the active control conditions they will complete only one of them (enhancing self-efficacy or perceived social support). Each module contains three evidence-based, CBT-framed exercises. Therefore, participants in the experimental conditions will be offered six exercises spaced out over 6 weeks, while the participants in the active controls will be presented with three exercises over the span of 3 weeks. Each exercise will be released once a week and users can work on them at their own pace. Participants will be encouraged to do all tasks, but the new exercise will be made available regardless of the completion of the previous one. Each exercise in each module is preceded with a psychoeducation part delivered via a short, animated movie. Participants will not need to watch the movies in order to complete the exercises, they will be only encouraged to do so. Completion of each model - defined as watching the movie, reading the instructions, and providing written responses online - takes about 1.5 h of screen time per week. Some of the exercises (i.e., *vicarious experience and action planning*) require performing actions away from the computer - in their work environment - and one exercise (*social skills and peer support*) necessitates longer screen time to take part in the forum discussion. Additionally, participants will have the option of benefitting from four additional modules at any time during the intervention.

#### Experimental condition: self-efficacy and perceived social support enhancement modules (cultivation hypothesis)

This experimental condition reflects the cultivation hypothesis and comprises two sequential modules with a self-efficacy enhancement module (SE) preceding a perceived social support enhancement module (SS). The SE module includes the following exercises: (1) *mastery experience* in which participants will recall own previous successes at work and identify coping mechanisms that could be used in the future, (2) *vicarious experience* in which participants will be encouraged to find a person at work that they identify with (a model) and recognize that person’s coping mechanisms that could be transplanted into their own life, and (3) *action planning* in which participants will create a plan and identify barriers and ways to overcome them using an “if-then” approach. The SS module includes the following exercises: (1) *received support & cognitive distortions* in which participants will identify situations when help was received, recognize cognitive distortions, and learn about their mechanisms, 2) *social skills & peer support* in which participants will receive and provide support for the other trial participants during a forum discussion in a private (3–4 users) chatroom, and (3) *action planning* in which participants will create a plan and identify barriers and ways to overcome them using an “if-then” approach. This condition lasts 6 weeks: each exercise will be released at the beginning of each week. Moreover, participants will have the option to engage in one or more out of four additional modules: relaxation, mindfulness, cognitive restructuring, and lifestyle.

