### Sample size

The study will be conducted among professionally active health professionals at risk of job stress and burnout. Bonferroni’s adjustment for multiple comparisons will be applied: there will be a comparison between the two experimental conditions and between each experimental condition and each active control condition giving a total of five comparisons posttest. Furthermore, we will include five outcomes. Taken together, this will lower *p* levels to .002. Meta-analyses of the effectiveness of web-based interventions for stress reduction found a small effect of *g* = 0.30 [19] for work-related stress, and a medium size effect of *d* = 0.49 for general stress [43]. Taking into account the minimum effect size of *d* = 0.20, in analysis of covariance (ANCOVA) with a significance level of α = 0.002, statistical power of 0.90, and the number of conditions (two experimental conditions and two active controls), a total of 607 participants will be set (152 participants per condition). Furthermore, a high dropout rate is usually encountered in unguided interventions (between 5 and 45%; [44]) and thus we ultimately plan for a sample of 1200 participants (300 participants per condition).

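### Three of the four arms meet in chatrooms of 3–4, but the ANCOVA and sample size treat participants as independent, so the actual error rate at the 0.002 threshold may differ from 0.002

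*Protocol article*

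**What the plan says.** Participants are randomised individually, 1:1:1:1. The social support (SS) module is described under the first experimental condition. In its second exercise "participants will receive and provide support for the other trial participants during a forum discussion", in a private room of 3–4 users. The second experimental condition uses the same two modules in reverse order, and the SS active control uses the same SS exercises. The self-efficacy (SE) active control receives only the SE module, which contains no forum. The Procedure section confirms the count: the Monday release is adopted because one exercise "requires participants in three conditions (those that include a perceived social support enhancement module) to take part in a forum discussion at the same time".

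The Statistical analysis section states: "We will conduct analyses of covariance (ANCOVA) with condition assignment as a factor", with the pretest value as covariate and separate ANCOVAs at 6 and 12 months. Mediation and moderation analyses are also planned. No room term is described for any of them.

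The Sample size section counts contrasts "giving a total of five comparisons posttest" and adds "Furthermore, we will include five outcomes", which leads to 0.002. It then sizes an ANCOVA "with a significance level of α = 0.002, statistical power of 0.90", arriving at 607 participants, raised to 1200 for dropout. The article contains no ICC and no design effect, and does not say how rooms are composed.

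**The concern.** The chatroom is meant to make its members influence one another, and perceived social support is both a target of the intervention and a hypothesised mediator. Outcomes of people who shared a room may therefore be correlated. Individual randomisation does not remove this, because the grouping arises during treatment. It arises in three arms and not in the fourth, which is a partially nested design.

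An ANCOVA that ignores rooms computes standard errors as if every participant were a separate unit. If rooms are formed within arm and the correlation is positive, those standard errors are too small and each test rejects more often than its nominal level. The protocol chose a strict per-test level in order to cover 25 tests, so the control it claims depends on that level being met.

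**Working it through.** **1. The threshold.** 0.05/(5 comparisons × 5 outcomes) = 0.05/25 = 0.002. The division is correct.

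**2. The stated sample size.** Noncentral F, four groups, one covariate, numerator df 3, alpha 0.002: power is 0.8995 at N = 606 and 0.9002 at N = 607. The stated 607 is reproduced exactly, with 0.20 entered as Cohen's f and with no clustering term. (The protocol labels the 0.20 as *d*. That is a separate matter.)

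**3. Actual error rate, rooms within arm, full attendance.** Room size m = 3 or 4 comes from the protocol. The ICC, meaning the correlation left after adjustment for the pretest value, is an assumption of 0.01 to 0.10.

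- Chatroom arm: DE = 1 + (m − 1) × ICC. SE-only arm: DE = 1.
- A contrast between equal-sized arms uses the mean of its two design effects.
- Actual alpha = 2 × [1 − Φ(3.090/√DE)].

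Example, m = 4 and ICC 0.05: DE = 1 + 3 × 0.05 = 1.15, and 3.090/√1.15 = 2.88, so alpha = 0.0040. Against SE-only: DE = (1.15 + 1)/2 = 1.075, so alpha = 0.0029.

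| m | ICC | DE, both arms with rooms | alpha | DE, against SE-only | alpha |
|---|---|---|---|---|---|
| 3 | 0.01 | 1.02 | 0.0022 | 1.01 | 0.0021 |
| 4 | 0.01 | 1.03 | 0.0023 | 1.015 | 0.0022 |
| 3 | 0.05 | 1.10 | 0.0032 | 1.05 | 0.0026 |
| 4 | 0.05 | 1.15 | 0.0040 | 1.075 | 0.0029 |
| 3 | 0.10 | 1.20 | 0.0048 | 1.10 | 0.0032 |
| 4 | 0.10 | 1.30 | 0.0067 | 1.15 | 0.0040 |

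A simulation with rooms of 4 and 152 per arm gave 0.0038 (ICC 0.05) and 0.0067 (ICC 0.10) with both arms clustered, and 0.0029 and 0.0036 with one arm clustered.

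**4. All 25 tests.** Of the five contrasts, three compare two chatroom arms (each experimental arm with SS-only, and the experimental arms with each other). Two compare an experimental arm with SE-only. For m = 4 and ICC 0.05, the Bonferroni bound is 5 × (3 × 0.00396 + 2 × 0.00288) = 0.088. It is about 0.057 at ICC 0.01 and 0.14 at ICC 0.10. The bound is conservative. In a simulation of all 25 tests with rooms of 4 and an assumed correlation of 0.5 between outcomes, the family-wise error was 0.040 without clustering, 0.045 at ICC 0.01, 0.067 at 0.05 and 0.100 at 0.10.

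**5. Partial attendance.** If a share p joins a room, DE = 1 + p(m − 1) × ICC. With p = 0.5 (assumed), m = 3.5 and ICC 0.05, DE = 1.0625 and alpha = 0.0027. Against SE-only, DE = 1.031 and alpha = 0.0023.

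**6. Rooms that mix arms.** Suppose each room holds k members of each of two compared arms. Each arm mean then has DE = 1 + (k − 1) × ICC, and the covariance between the arm means subtracts k × ICC, so the contrast has DE = 1 − ICC. At ICC 0.05 this is 0.95, alpha = 0.0015, and the ordinary standard error is about 2.6% too large (1/√0.95 = 1.026). This applies to contrasts between chatroom arms. Contrasts with SE-only keep 1 + (k − 1) × ICC in the chatroom arm.

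**7. Effect on the sample size.** With 152 per arm and rooms of 4, the required total is 152 + 3 × 152 × (1 + 3 × ICC) = 608 + 1368 × ICC: about 622, 676 and 745 at ICC 0.01, 0.05 and 0.10. At the highest cited dropout of 45%, 1200 × 0.55 = 660 remain, which covers an ICC up to (660 − 608)/1368 = 0.038 on the protocol's own basis.

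**The case against.** The strongest case on the other side is that the effect may be slight. Rooms are small, the forum is one of three exercises in the SS module, and the next exercise is released whether or not the previous one was done. The Discussion itself expects adherence and dropout problems. Participants who never join a room stay in the intention-to-treat analysis without adding room correlation. No ICC is documented, and at 0.01 the effect is negligible. All of this stands and limits the size of the point.

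It can also be said that a condensed article leaves covariance structures and sensitivity models to the analysis plan. That holds in part. But the article does fix the model, covariate, multiplicity rule and imputation, and the model it fixes does not match the intervention it describes. Room membership must also be captured during the trial; a later plan cannot recover it if it was not saved.

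A reader might infer three stronger things that the protocol does not support:

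- **That the 0.002 threshold is miscalculated.** It is not (step 1).
- **That every analysis is an ordinary ANCOVA.** Mediation and moderation analyses are planned as well, though no room term is described for them either.
- **That rooms do combine arms.** The Procedure section says that three conditions take part at the same time, in order to explain the Monday release. It does not say who shares a room. The forum exercise falls in week 2 of the SS-first and SS-only arms and week 5 of the SE-first arm. With continuous enrolment, mixing is possible but not stated.

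**Conclusion.** The point holds in a limited form. The design is partially nested, and the stated ANCOVA and sample size ignore this. With rooms of 3–4 formed within arm and full attendance, the actual per-test error rate stays near 0.002 at an ICC of 0.01, rises to roughly 0.003–0.004 at 0.05, and lies between 0.0032 and 0.0067 at 0.10. Partial attendance brings these figures down. Every ICC here is an assumption.

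It would go too far to say that the standard errors are known to be too small. That requires a positive correlation within rooms and rooms formed within arm, and the protocol establishes neither. If rooms mix arms, contrasts between chatroom arms could be conservative instead. Under either arrangement, an ANCOVA without a room term does not represent the dependence.

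**What to change.** Record the chatroom of each participant who joins one. Then do one of the following:

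- keep the planned ANCOVA contrasts and compute their standard errors clustered on room, with SE-only participants and non-attenders as singletons; or
- fit a partially nested mixed model with a random room effect only for chatroom participants.

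Apply the same approach to the 6- and 12-month ANCOVAs. State in the plan whether rooms are arm-specific.

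Clustering on room is valid whether or not rooms mix arms, so the fix does not require same-arm rooms. Waiting to fill such rooms could disturb the fixed Monday release.

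The cost is one extra stored variable and a changed model line. The article does not say whether the platform already keeps a room identifier, so this should be checked before enrolment. Intervals become slightly wider if the ICC is positive: standard errors grow by about 7% for contrasts between two chatroom arms at rooms of 4 and ICC 0.05 (√1.15 = 1.072). If the ICC is near zero, the results barely change.
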